## Abstract

**Background:**

Although many studies have reported the biological basis of major depressive disorder (MDD), none have been put into practical use. Recently, we developed a generalizable brain network marker for MDD diagnoses (diagnostic marker) across multiple imaging sites using resting-state functional magnetic resonance imaging (rs-fMRI). We have planned this clinical trial to establish evidence for the practical applicability of this diagnostic marker as a medical device. In addition, we have developed generalizable brain network markers for MDD stratification (stratification markers), and the verification of these brain network markers is a secondary endpoint of this study.

**Methods:**

This is a non-randomized, open-label study involving patients with MDD and healthy controls (HCs). We will prospectively acquire rs-fMRI data from 50 patients with MDD and 50 HCs and anterogradely verify whether our diagnostic marker can distinguish between patients with MDD and HCs. Furthermore, we will longitudinally obtain rs-fMRI and clinical data at baseline and 6 weeks later in 80 patients with MDD treated with escitalopram and verify whether it is possible to prospectively distinguish MDD subtypes that are expected to be effectively responsive to escitalopram using our stratification markers.

**Discussion:**

In this study, we will confirm that sufficient accuracy of the diagnostic marker could be reproduced for data from a prospective clinical study. Using longitudinally obtained data, we will also examine whether the “brain network marker for MDD diagnosis” reflects treatment effects in patients with MDD and whether treatment effects can be predicted by “brain network markers for MDD stratification”. Data collected in this study will be extremely important for the clinical application of the brain network markers for MDD diagnosis and stratification.

**Trial registration:**

Japan Registry of Clinical Trials (jRCTs062220063). Registered 12/10/2022.

## Background

Major depressive disorder (MDD) is a psychiatric disorder characterized by a depressed mood, decreased motivation/interest/mental activity, decreased appetite, sleeplessness, and persistent sadness/anxiety. MDD leads to the largest social loss among all illnesses [1, 2]. However, the development of treatments for psychiatric disorders is stagnant, and one of the contributory factors is the limited objective diagnostic methods.

The Diagnostic and Statistical Manual of Mental Disorders (DSM) provides a common language and standard criteria for classifying and diagnosing psychiatric disorders. The diagnosis of MDD is also defined in the DSM. However, the diagnosis depends on the physician’s subjective judgment of clinical symptoms, and the reliability of the diagnosis is considered to be inadequate even with the latest diagnostic criteria, the DSM-5. The concordance rate between testers for MDD diagnosis is very low, with a κ coefficient of 0.28, therefore establishing an objective diagnosis is an urgent issue [3].

Furthermore, MDD diagnosed based on the DSM is not a biologically homogeneous group, and it is considered that different treatments according to the MDD subtypes are required. In fact, it is known that the remission rate for drug therapy is approximately 30% for first-line antidepressants and < 70% even with the use of various treatments [4]. However, no stratification method currently exists to identify a biologically uniform MDD subtype that responds to a particular drug therapy.

Although many studies have reported the biological basis of psychiatric disorders, none have been put into practical use or are useful in clinical practice. Particularly, resting-state functional magnetic resonance imaging (rs-fMRI) is expected to be put into practical use owing to its safety and provision of a large amount of information. However, there is a great difficulty in practical use because the nature of the data differs depending on the measurement facility. Therefore, we integrated rs-fMRI data acquired at multiple institutions by the harmonization method using traveling individuals as homogeneous large-scale data (total of 1,584 cases) [5] and subsequently applied a cutting-edge machine learning method to develop a brain network marker for MDD diagnosis [6]. This brain network marker can distinguish between healthy individuals and patients with MDD with a probability of approximately 70%, even for completely independent data obtained at different facilities [6]. Therefore, we designed this study as a clinical trial to establish anterograde evidence for the practical application of this brain network marker for MDD diagnosis (diagnostic marker) as Software as a Medical Device. In addition, we developed brain network markers for MDD stratification (stratification marker) with robustness among independent datasets by performing unsupervised machine learning on rs-fMRI data of patients with MDD [7]. Statistically significant differences were also observed in the therapeutic responsiveness to escitalopram between the MDD subtypes discriminated by these brain network markers. Therefore, the anterograde verification of these stratification markers was set as the secondary endpoint of this study. The results of this study will provide useful information for the diagnosis and treatment selection of MDD using rs-fMRI.

## Methods/Design

### Study design and setting

This study will be a non-randomized, open-label study involving patients with MDD and healthy controls (HCs).

This trial will be conducted at eight facilities (Hiroshima University Hospital, Kabe Mental Health Clinic, Minna no Suimin Stress Care Clinic, Mantani Mental Clinic, Ujina Mental Clinic, Yokota Mental Clinic, Tamura Mental Clinic, and Jitsuiki Clinic) in Japan.

Three groups of patients with MDD will be enrolled in this study. The first group will continue treatment with escitalopram only for at least the first 6 weeks but will be followed for a total of 6 months without other restrictions on antidepressant treatment (escitalopram group); the second group will receive regular medical care (no restrictions on antidepressant medication) for 6 months and obtain data longitudinally (usual care group); the third group will acquire data only at one point for a cross-sectional study (cross-sectional study group). In addition, for HCs, only one data point will be used. MRI and clinical evaluations in each group will be performed according to the schedule presented in Tables 1, 2 and 3.

**Table 1 Tab1:** Schedule of escitalopram group and usual care group

Timing Item	Registration date	First measurement date of the MRI	Outpatient examination		
			Consultation day	After 6 weeks	After 6 months
Schedule	-1 week	0 week	N/A^b^	6th week	24th week
Allowance from the specified date	± 1 week	0		± 2 weeks	± 4 weeks
Consent	**○**				
Background information	**○**				
PHQ-9	**○**			**○**	**○**
BDI-II	**○**		**○**	**○**	**○**
DSM-5 (MINI)	**○**				
HRSD		**○**		**○**	**○**
YMRS		**〇**		**〇**	**〇**
SHAPS, PANAS		**○**		**○**	**○**
NEO-FFI, CATS	**○**^a^				
JART, handedness		**○**			
MRI		**○**		**○**	**○**
Medication status	**○**	**○**	**○**	**○**	**○**
Evaluation of adverse events	**○**	**○**	**○**	**○**	**○**

^a^It will be distributed on the day of consent acquisition and can be collected at week 0

^b^No interval is specified to match the schedule of usual medical care

*BDI-II* Beck Depression Inventory-II, *CATS* Child Abuse and Trauma Scale, *DSM-5* Diagnostic and Statistical Manual of Mental Disorders 5th edition, *HRSD* Hamilton Rating Scale for Depression, *JART* Japanese Adult Reading Test, *MINI* Mini-International Neuropsychiatric Interview, *Neo-FFI* Neo-Five-Factor Inventory, *PANAS* Positive and Negative Affect Schedule, *PHQ-9* Patient Health Questionnaire-9, *SHAPS* Snaith-Hamilton Pleasure Scale, *YMRS* Young Mania Rating Scale, *HRSD* Hamilton Rating Scale for Depression

**Table 2 Tab2:** Schedule of the cross-sectional study group

Timing Item	Registration date	Measurement date of MRI
Schedule	-1 week	0 week
Allowance from the specified date	± 1 week	0
Consent	**○**	
Background information	**○**	
BDI-II	**○**	
DSM-5 (MINI)	**○**	
HRSD		**○**
YMRS		**〇**
CATS	**○**^a^	
handedness		**○**
MRI		**○**
Medication status	**○**	**○**
Evaluation of adverse events	**○**	**○**

^a^It will be distributed on the day of consent acquisition and can be collected at week 0

*BDI-II* Beck Depression Inventory-II, *CATS* Child Abuse and Trauma Scale, *DSM-5* Diagnostic and Statistical Manual of Mental Disorders 5th edition, *MINI* Mini-International Neuropsychiatric Interview, *HRSD* Hamilton Rating Scale for Depression, *MRI* magnetic resonance imaging

**Table 3 Tab3:** Schedule of healthy controls

Timing Item	Registration measurement date of MRI
Schedule	0 week
Consent	**○**
Background information	**○**
BDI-II	**○**
DSM-5(MINI)	**○**
CATS	**○**
handedness	**○**
MRI	**○**
Evaluation of adverse events	**○**

*BDI-II* Beck Depression Inventory-II, *CATS* Child Abuse and Trauma Scale, *DSM-5* Diagnostic and Statistical Manual of Mental Disorders 5th edition, *MINI* Mini-International Neuropsychiatric Interview, *MRI* magnetic resonance imaging

This trial was registered at jRCT (jRCTs062220063) on 12/10/2022 and will adhere to the Standard Protocol Items: Recommendations for Interventional Trials guidelines [8].

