### Purposes of the study

The purposes of this study are as follows:

Purpose 1. We will verify whether it is possible to distinguish between patients with MDD and HCs using a “diagnostic marker.”Purpose 2. We will examine whether this “diagnostic marker” reflects the effects of treatment in patients with MDD.Purpose 3. We will longitudinally obtain data on patients with MDD treated with escitalopram and verify whether it is possible to distinguish MDD subtypes that are related to escitalopram treatment response using “stratification markers.”Purpose 4. We will examine whether treatment effects can be distinguished by “stratification markers” for drug therapies other than escitalopram.Purpose 5. We will use the MRI data obtained in the verification process as learning data for the updated Artificial Intelligence (AI) program that assists in diagnosing MDD for accuracy improvement.

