### Primary and secondary endpoints

The primary endpoint will be the area under the curve (AUC) of the receiver operating characteristic (ROC) curve when distinguishing between patients with MDD and HCs using the depression probability value calculated from the diagnostic marker at week 0.

The following will be the secondary endpoints:

Longitudinal evaluation of the diagnostic marker: The depression probability value, which is the output of the diagnostic marker, will be analyzed with two factors: remission/non-remission and time of treatment (0 w, 6 w, 6 m). Remission has been defined as a depression severity of 7 points or less using the Hamilton Rating Scale for Depression (HRSD).Depression severity will be obtained longitudinally (0 w, 6 w) in the escitalopram group; we will compare the rate of symptom improvement evaluated using the HRSD among the subtypes identified by the stratification markers in the escitalopram group.Depression severity will be obtained longitudinally (0 w, 6 w) in the usual care group, and we will compare the rate of symptom improvement evaluated using the HRSD among the subtypes identified by the stratification markers in the usual care group.

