### Allocation

Patients with MDD who consent to participate in this study will be assigned to either the escitalopram group, usual care group, or cross-sectional study group based on the following criteria during enrollment. The applicability of each group will be confirmed in the following order: escitalopram group, usual care group, and cross-sectional study group.

The inclusion criteria for the escitalopram group will be as follows: (1) no treatment or less than 2 weeks of antidepressant treatment with an escitalopram-equivalent dose of 5 mg/day or less during the current depressive episode, and (2) patients who are suitable to start treatment with escitalopram based on the clinical judgment of a physician.

The exclusion criteria of the escitalopram group will be as follows: (1) use of mood stabilizers and antipsychotics; (2) receiving electroconvulsive therapy within 3 months before informed consent; (3) receiving standardized psychotherapy (including cognitive-behavioral therapy and interpersonal therapy) other than standard outpatient psychotherapy; and (4) contraindications for escitalopram.

The inclusion criteria of the usual care group will be as follows: (1) no treatment or less than 2 weeks of antidepressant treatment with an escitalopram-equivalent dose of 5 mg/day or less during the current depressive episode; (2) not meeting the inclusion criteria for the escitalopram group or inability to continue escitalopram treatment for 6 weeks.

The exclusion criteria for the usual care group will be as follows: (1) use of mood stabilizers and antipsychotics; (2) receiving electroconvulsive therapy within 3 months before informed consent; and (3) receiving standardized psychotherapy other than standard outpatient psychotherapy.

Regarding the cross-sectional study group, among the patients who meet the participation criteria for this study, those who do not meet the selection criteria for either the escitalopram group or the usual care group are eligible.

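### The 6-week HRSD may be taken as late as week 8, but the escitalopram-only rule need run only 6 weeks, so a compliant response rating can follow a change of treatment

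*Protocol article*

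**What the plan says.** Protocol article, Study design and setting: the escitalopram group "will continue treatment with escitalopram only for at least the first 6 weeks". Follow-up then runs to 6 months with antidepressant choice otherwise open.

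Table 1, same section: the row "Allowance from the specified date" gives ± 2 weeks for the visit at the 6th week. HRSD and MRI are scheduled at week 0, at that visit and at 6 months. Between week 0 and the 6-week visit there are only consultation days, for which footnote b says "No interval is specified to match the schedule of usual medical care". Those days collect BDI-II, medication status and adverse events, but no HRSD.

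Purposes of the study, Purpose 3: the aim is to "verify whether it is possible to distinguish MDD subtypes that are related to escitalopram treatment response". Purpose 4 deals separately with other drug therapies.

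Primary and secondary endpoints: using HRSD at 0 w and 6 w, "we will compare the rate of symptom improvement evaluated using the HRSD among the subtypes identified by the stratification markers in the escitalopram group".

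Allocation: the one nearby provision makes "inability to continue escitalopram treatment for 6 weeks" a route into the usual care group. It does not address the time between week 6 and a later rating. Analysis of secondary endpoints tests the subtype comparison at 5% and puts no condition on treatment at the time of the rating.

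**The concern.** The escitalopram-only period exists so that the HRSD change can be read as response to escitalopram. The visit window extends past the end of that period. A physician may switch or add a drug once the 6 weeks are over, and the patient may then be rated up to week 8, with no stated rule broken. That rating enters the Purpose 3 comparison as escitalopram response, although part of it reflects a treatment that belongs under Purpose 4.

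Poor responders are the patients most likely to have treatment changed, which is a clinical expectation and not a statement in the article. If so, ratings taken after a change would tend to blur a difference between subtypes. An analysis plan can identify such ratings, because medication status is recorded. It cannot supply an HRSD from before the change if none was taken. That part can be dealt with only in the conduct rules.

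**Working it through.** **Inputs**
- Minimum escitalopram-only period: 6 weeks (Study design and setting).
- 6-week visit: week 6 ± 2 weeks, counted from the first MRI at week 0 (Table 1).
- Antidepressant treatment before enrolment: none, or less than 2 weeks at a low dose (Allocation).
- Subtype comparison: 68 patients required, about 10% loss expected, 80 to be registered (The target number of participants and the basis for setting).

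**Visit window**
- Earliest rating: 6 − 2 = week 4.
- Latest rating: 6 + 2 = week 8.

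**Time not covered by the escitalopram-only rule.** Let *s* be the week, relative to week 0, at which the 6 weeks start to count. The article does not state it. The earliest permitted change is then at week *s* + 6.

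- Uncovered time before the latest rating = 8 − (*s* + 6) = 2 − *s* weeks.
- Part of the visit window lying before the earliest permitted change = (*s* + 6) − 4 = 2 + *s* weeks.

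| Assumed *s* | Uncovered time | Window before the earliest change |
|---|---|---|
| −1 (drug started a week before the MRI) | 3 weeks | 1 week |
| 0 (week 0, the natural reading of Table 1) | 2 weeks | 2 weeks |
| +1 (drug started a week after the MRI) | 1 week | 3 weeks |

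With *s* = 0, the uncovered time is 2 × 7 = 14 days out of 8 × 7 = 56, or 25% of the time to the latest rating. This is a calendar limit, not an estimate of bias. The values −1 and +1 are illustrations. Both directions are possible, since Allocation permits some treatment before enrolment and the article does not fix the date of the first dose.

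**Do other sections close the gap?** Allocation addresses failure to complete 6 weeks. The endpoint and analysis sections define the comparison by time point and group. None requires the rating to come before a change.

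**Room to exclude affected ratings.** 80 × 0.90 = 72 evaluable, against 68 required. The margin is 72 − 68 = 4, and 4/72 = 5.6%. Excluding more than 4 ratings would fall below the stated requirement. This argues against exclusion by default; it does not measure the problem.

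**What cannot be computed.** The article gives no rate of late visits, no rate of treatment changes between weeks 6 and 8, and no effect of such a change on HRSD. Any power loss would rest wholly on assumed values.

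**The case against.** **The two rules do not conflict.** A reader might infer a contradiction. There is none: the drug rule is a minimum, the ± 2 weeks is a scheduling tolerance, and a patient who stays on escitalopram until a late visit satisfies both. What stands is that nothing stated requires this.

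**The 6 weeks may mean the 6-week visit.** The abstract says "we will longitudinally obtain rs-fMRI and clinical data at baseline and 6 weeks later in 80 patients with MDD treated with escitalopram", and Table 1 labels the visit as the one after 6 weeks. Escitalopram only up to that assessment may be what was intended. The text does not exclude this reading, but it does not state it either, and a site could act on the calendar reading. The objection supports treating the point as a clarification.

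**A condensed article leaves such detail to the full protocol.** This has weight: the order of visit and drug change may be settled there, and handling of affected ratings is ordinary material for an analysis plan. The point rests on two rules that the article does state, with numbers, and that together permit the sequence. If the full protocol already orders the visit first, the article needs only to say so.

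**No effect is shown.** Correct. Harm needs a visit after week 6, a change before that visit, and enough HRSD movement in a short time. A reader might infer that the subtype comparison is biased or loses a known amount of power. The article gives no figure that would support that.

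**Conclusion.** The point holds as a minor one. Under the stated rules, a compliant 6-week HRSD for the escitalopram-response comparison can follow a switch or add-on. Counted from week 0, up to 2 weeks of changed treatment can precede it. That figure depends on an anchor the article leaves open, so it should not be quoted as a firm maximum, and 6 weeks of escitalopram alone from week 0 should not be taken as guaranteed. Frequency and effect are unknown. Only a secondary endpoint is touched, and only in patients whose treatment has changed before a late rating. The primary AUC uses week 0 data and is not involved. The correction is worth making because it is cheap and because an HRSD not taken before a change cannot be recovered later.

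**What to change.** Add one sentence to Study design and setting and a footnote to Table 1:

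- In the escitalopram group, the 6-week visit, with HRSD and MRI together, is to be done before any change from escitalopram-only treatment. If a change is planned, the visit is brought forward within the existing week 4 to 8 window.
- State whether the 6 weeks count from week 0 or from the first dose.
- Where clinical need means the change comes first, the physician proceeds. The rating is flagged from the medication status already recorded, and the subtype comparison is reported with and without flagged ratings.

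This puts the visit first without making escitalopram alone compulsory up to week 8. HRSD and MRI should stay together because the 6-week HRSD also defines remission for the analysis of the depression probability value over time.

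The cost is small: no new visit, scan or instrument, and no change to the sample size. Patients come from eight facilities but are scanned only at Hiroshima University, so some visits will need rescheduling and some will not be movable in time. Bringing visits forward also gives some poor responders a slightly shorter time to rating, within the allowance the protocol already accepts.

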### Purposes of the study

The purposes of this study are as follows:

Purpose 1. We will verify whether it is possible to distinguish between patients with MDD and HCs using a “diagnostic marker.”Purpose 2. We will examine whether this “diagnostic marker” reflects the effects of treatment in patients with MDD.Purpose 3. We will longitudinally obtain data on patients with MDD treated with escitalopram and verify whether it is possible to distinguish MDD subtypes that are related to escitalopram treatment response using “stratification markers.”Purpose 4. We will examine whether treatment effects can be distinguished by “stratification markers” for drug therapies other than escitalopram.Purpose 5. We will use the MRI data obtained in the verification process as learning data for the updated Artificial Intelligence (AI) program that assists in diagnosing MDD for accuracy improvement.

### Primary and secondary endpoints

The primary endpoint will be the area under the curve (AUC) of the receiver operating characteristic (ROC) curve when distinguishing between patients with MDD and HCs using the depression probability value calculated from the diagnostic marker at week 0.

The following will be the secondary endpoints:

Longitudinal evaluation of the diagnostic marker: The depression probability value, which is the output of the diagnostic marker, will be analyzed with two factors: remission/non-remission and time of treatment (0 w, 6 w, 6 m). Remission has been defined as a depression severity of 7 points or less using the Hamilton Rating Scale for Depression (HRSD).Depression severity will be obtained longitudinally (0 w, 6 w) in the escitalopram group; we will compare the rate of symptom improvement evaluated using the HRSD among the subtypes identified by the stratification markers in the escitalopram group.Depression severity will be obtained longitudinally (0 w, 6 w) in the usual care group, and we will compare the rate of symptom improvement evaluated using the HRSD among the subtypes identified by the stratification markers in the usual care group.

